#### 7.5 No incentive (standard of care, information group)

In the no incentive/standard of care arm, study staff will inform participants of the importance of frequent testing for HIV as per Uganda Ministry of Health guidelines for high-risk populations, and to test for HIV at a study-testing facility at a certain interval (e.g. 1, 3 months). The no incentive arm will serve as a comparison to both the loss-framed and gain-framed incentives described above.

#### 7.6 Outcome measures

##### Primary outcomes:

- a) **Feasibility and acceptability of deposits.** We will record the number of eligible adults that agree to continue to participate in the pilot trial by incentive arm, following randomization. We will also record whether a participant randomized in the loss-aversion arms makes a deposit. We will also conduct qualitative interviews to understand why a participant agreed or declined to make a deposit, and the *mechanisms* through which deposits succeeded or failed in promoting repeat HIV testing (see Section 7.6.2).

##### Secondary outcomes:

- a) **HIV testing uptake.** We will record whether each study participant tested for HIV at a study-testing venue (see Section 7.6.1 below) within a period of about 1-3 months after randomization. We will use electronic fingerprint biometric measurements that link participants in real-time to a study ID at the time of HIV testing to determine whether study participants tested for HIV or not. We will compare HIV testing uptake to better inform sample size (power) calculations for planning of a larger trial of loss aversion incentive strategies to promote repeat HIV testing.
- b) **HIV test result** of each participant who gets tested.

Predictors and mediators: Participants' demographic and socio-economic characteristics, as well as HIV risk behaviors, will be recorded at the time of the baseline HIV test.

## 7.6.1 HIV Testing

### 7.6.1.1 Testing Venues

We will measure HTC at one or more venues within each study community. These may include the community's government-run health facility or at mobile testing sites established by our study (see Section 5.6.1). HTC uptake will be recorded at baseline and over a period of up to 3 months after enrolment and randomization.

At the time they are enrolled in the study, all participants will receive information on when and where to find the testing venues where repeat HTC uptake will be recorded.

### 7.6.1.2 Testing Procedures

Pre-test counseling: Prior to undergoing diagnostic testing, pre-test counseling will take place to inform and update participants on the diagnostic services offered and to answer questions.

HIV Testing: Rapid HIV Antibody testing for all participants will take place according to Uganda MoH policy and using the MoH HIV testing algorithm [54]:

1. Initial rapid HIV test
2. All negative results will be informed of their HIV-negative status
3. All positive results will be confirmed with a second rapid HIV test, performed either in series or in parallel with the first test.
4. Discordant results (first test positive, second test negative): participants with discordant rapid tests will undergo a third "tie-breaker" HIV rapid test. Participants with a positive "tie-breaker" test will be informed that they are HIV positive. Participants with a negative "tie-breaker" test will be told that their results are negative.

Non-HIV Health Services: The following services, delivered according to MoH guidelines (and many of which we have implemented in prior studies [28, 53] and the ongoing SEARCH Trial), may be offered at mobile HIV testing sites:

- *Recommended:* Finger-stick blood glucose measure
- *Recommended:* Syphilis screening (RPR)
- *Recommended:* Blood pressure measurement
- *Recommended:* HIV-infected participants: HIV RNA ("viral load") and point-of-care CD4 cell count testing
- *Recommended:* Malaria rapid diagnostic test (RDT) participants with objective fever ( $\geq 38.5$  degrees Celsius)
- *Recommended:* TB screening (sputum collection for microscopy, *Mycobacterium tuberculosis* culture, or other Uganda MoH approved sputum tests) for all individuals.

Post-test Counseling: All participants, regardless of test results, will receive post-test counseling. Individuals who test HIV positive will be immediately offered referral to a clinic that provides ART and counseled as per Uganda MOH guidelines.

Post-test Questionnaire: Participants who come for repeat testing (i.e. 1-3 months after baseline HIV testing) will be asked to participate in a short questionnaire to understand their reasons for testing. Participants who do not come for repeat testing will be contacted and asked to participate in a short questionnaire to understand their reasons for not testing.

## 7.6.2 Qualitative interview

In-depth semi-structured interviews: We will conduct semi-structured interviews on proportion of study participants in each study arm and subgroup. These interviews will seek to understand the *mechanisms* through which incentives succeeded or failed.

The interview guide will elicit participants' perceptions, attitudes, and preferences related to incentives, including deposits, and psychosocial and contextual factors that influence participants' responses to these incentives and the decision whether or not to test for HIV.

## 7.7 Data Management and Statistical Considerations

### 7.7.1 Data Collection & Management

Staff will record all study questionnaire data, HIV test results, and clinic data under each participant's study identification number (ID) in either paper lab logs or password-protected study computers. In-depth semi-structured interviews may be audio recorded. Data from these logs or devices will be entered and transferred via a secure electronic transfer to our data center facility in Kampala and stored on a secure server.

### 7.7.2 Analysis

#### Primary analysis:

- (a) ***Feasibility and acceptability:*** We will determine the proportion of individuals who agree to make a deposit in the loss aversion-based incentive group, and compare this to the proportion of randomized persons who agree to participate in the gain-framed incentive and no incentive groups following randomization. For qualitative interviews, data collection and analyses will be similar to those described in Section 5.7.2.

#### Secondary analyses:

- (a) ***HIV testing uptake:*** We will compare HTC uptake between the study groups. We hypothesize that HTC uptake among participants offered loss aversion incentives would be higher than uptake among men offered no incentive. We will test for significant differences in HTC uptake between the following groups using the 2-tailed  $\chi^2$  analysis or other appropriate statistical methods: a) loss aversion vs. gain-framed incentive; b) loss aversion vs. no incentive; and c) gain-framed vs. no incentive.
- (b) ***HIV incidence:*** We will compare the proportion of HIV testers who are newly diagnosed as HIV positive in each of the study groups using 2-tailed  $\chi^2$  tests or other appropriate statistical methods.

### 7.7.3 Sample Size & Accrual

The pilot trial will have about 120 total participants, with 25 participants in the no incentive arm, 25 in the gain-framed incentive arm, and about 50-70 participants in the loss-aversion group. The primary goal of the pilot is to gather preliminary data to inform intervention development (feasibility and acceptability) and sample size calculations for a larger trial in the future. In this pilot trial, we will compare the proportion of deposits made in the loss aversion subgroups and HTC uptake among all study groups.

## 8. Repeat HIV Testing Incentives Trial

### 8.1 Recruitment & Enrollment of Study Participants

#### 8.1.1 Recruitment

Prior to the start of the study, study team members will meet with local officials and community representatives to discuss the study and plans for recruiting individuals at higher-risk of HIV acquisition at social venues. In the selected venues (e.g. trading centers, bars, transport stages), study team members will provide information via pamphlets, flyers or postcards, on local HIV testing venues that potential participants may access. All individuals who subsequently come to the HIV testing venues and undergo an initial HIV test will be given cash or in-kind compensation of up to \$10 for their time and transport costs. This compensation will be provided to participants upon completion of the initial HIV testing.

Men and women who come to the testing venue and test HIV-negative will be recruited to enroll in the Repeat HIV Testing Incentives Trial. Following post-test counseling, study staff will describe the trial and proceed with obtaining written consent for enrollment from those who meet the eligibility criteria below. Persons who wish to consider enrolling in the trial at a later date will remain eligible for screening for enrollment in the Repeat HIV Testing Incentives Trial and receive information on how to contact study staff for enrollment at a later date.

#### 8.1.2 Consent Process

Study staff will review the informed consent form with recruited adults who meet the inclusion and exclusion criteria below and answer any questions about study participation. Eligible individuals who provide written consent to study enrollment will be administered a questionnaire and fingerprinted before being randomized.

#### 8.1.3 Screening for Enrollment

##### 8.1.3.1 Inclusion Criteria

- (a) HIV-negative by rapid HIV antibody test at time of recruitment;
- (b) Ages 18 – 59 years old;
- (c) Reported willingness to retest for HIV in the six months following recruitment;
- (d) Sexual risk behavior, defined as at least one of the following self-reported risks:
  - i) >1 partner in the 12 months prior to recruitment; or
  - ii) known HIV-infected sexual partner; or
  - iii) history of a sexually transmitted infection in the 12 months prior to recruitment; or
  - iv) paid or received compensation or gifts for sex in the 12 months prior to recruitment.

##### 8.1.3.2 Exclusion Criteria

- (a) Intention to move away from the community for  $\geq 4$  consecutive months during the six months following recruitment.
- (b) A history of testing for HIV  $\geq 3$  times in the 12 months prior to recruitment, by self-report

### 8.2 Randomization

Eligible participants will be randomized to one of three main arms: 1) a loss-aversion incentive in which participants will be asked to voluntarily make a deposit contract that can be retrieved if they retest for HIV in the future or can be lost if they do not retest; 2) a standard gain-framed incentive arm in which participants will be offered an incentive for retesting for HIV in the future; and 3) a no incentive (control) arm in which participants will be encouraged to retest for HIV in the future, but no incentives will be provided.

Randomization will occur as follows: study staff will provide participants previously block-randomized scratch cards or envelopes to determine which condition each participant receives. Study staff and participants will not know what study condition an individual is randomized to until the participant scratches the card. Eligible adults will be randomized to the three groups in a 1:1:1 ratio.

### 8.3 Gain-framed incentive (reward group)

Study staff will tell participants that they will receive an incentive payment if they retest for HIV within 3-4 months from the time of enrollment, and a second, equal incentive payment if they retest again (a second time) within 6-7 months from the time of enrollment. Each incentive amount will not exceed US\$15. Participants will be encouraged to come for HIV retesting in the future and told that they will receive the payments after undergoing each HIV test.

### 8.4 Loss aversion incentive (deposit contract group)

In the loss aversion arm, study staff will ask participants if they would like to make a deposit of a certain amount, not exceeding US\$15. The amount of compensation given to participants for participating in baseline HIV testing (as described above in 8.1.1 Recruitment) will facilitate the ability of interested participants to make a deposit, as we have learned in the pilot study we conducted in 2017. Study staff will retain deposits securely and participants will receive a receipt indicating their deposit amount. Participants will be able to retrieve their deposit when they return for HIV testing at the 3-month study visit. Participants who attend the 3-month visit and retest HIV negative will be asked if they would like to make a second deposit of a certain amount, not exceeding US\$15, to retest a second time at the 6-month study visit. In addition to retrieving their deposit if they return for HIV testing, participants will also receive interest (not exceeding US\$5 at each retest visit) on each of their deposits. The possibility that participants will lose their deposit if they do not come for an HIV test within the pre-specified testing periods (3-4 months, and 6-7 months after randomization) will be communicated clearly by study staff; deposits from individuals who do not test will be retained by the study team and will be used for other study-specific activities. This aspect of deposit contracts is essential in order for the principle of loss aversion to have an impact on participants' HIV testing behavior. Our pilot study in 2017 showed that a large majority of individuals were willing to make deposits and that the system of providing receipts worked well.

Adaptive intervention: Following enrollment of 20% of the anticipated number of participants in the loss aversion group, the study investigators will determine the proportion of participants who have agreed to make a baseline deposit. In the event that <15% of loss aversion incentive group participants have agreed to make a deposit, the study investigators may reduce the deposit amount by up to 50% in the loss aversion group for the remaining duration of the Aim 3 trial.

Study staff will emphasize the voluntary nature of the deposit contract and remind participants that they are not required to make a deposit. Participants who decline to provide a deposit at baseline will still be encouraged to come for an HIV test within the pre-specific testing periods (3-4 months, and 6-7 months), but will not receive any incentive for the return HIV test at 3-4 months. Participants who do not make a baseline deposit, but come for retesting at the 3-4 month visit, will have an opportunity to make a deposit at the 3-4 month visit to return for HIV retesting at 6-7 months.

### 8.5 No incentive (standard of care, information group)

In the no incentive (control) group, study staff will inform participants of the importance of frequent testing for HIV as per Uganda Ministry of Health guidelines for high-risk “key populations”, [60] and to test for HIV at a study-testing facility at 3 months and 6 months following randomization. The no incentive arm will serve as a comparison to both the loss aversion and gain-framed incentives described above.

### 8.6 Outcome measures

#### Primary outcome:

- a) **HIV retesting uptake at 3 and 6 months.** The primary outcome will be defined as the proportion of participants who retest for HIV at a study venue at both 3- and 6-month study visits. Successful retesting uptake will be defined as accessing HIV testing at a study-testing site (see Section 8.6.1 below) within 3-4 months and 6-7 months of randomization. We will use electronic fingerprint biometric measurements that link participants in real-time to a study ID at the time of HIV testing to determine whether study participants tested for HIV or not. Retesting outside of the pre-specified testing “windows” will not be considered as successful HIV retesting uptake.

## Secondary outcomes:

- b) **HIV retesting uptake at 3-4 months following randomization.**
- c) **HIV retesting uptake at 6-7 months following randomization.**
- d) **HIV retesting uptake among deposit contract group participants who make deposits.** We will evaluate HIV retesting uptake among participants in the deposit contract group who agree to make a baseline deposit, a 3-4 month deposit, and those who agree to make a deposit at both study baseline and the 3-4 month study visit.
- e) **Cumulative incidence of HIV seroconversion:** We will compare the cumulative incidence of HIV infections in each study group over the 6-7 months of study participation following randomization.

Predictors and mediators: Participants' demographic and socio-economic characteristics, as well as HIV risk behaviors, will be recorded at the time of the baseline HIV test.

## **8.6.1 HIV Testing**

### **8.6.1.1 Testing Venues**

We will measure HIV testing at one or more venues within each study community. These may include the community's government-run health facility or at mobile testing sites established by our study (see Section 5.6.1). HIV testing uptake will be recorded at baseline and over a period of up to 12 months after enrolment and randomization, in order to allow for follow up testing of participants who do not retest within 7 months of randomization.

At the time they are enrolled in the study, all participants will receive information on when and where to find the testing venues where HIV retesting uptake will be recorded.

### **8.6.1.2 Testing Procedures**

Pre-test counseling: Prior to undergoing diagnostic testing, pre-test counseling will take place to inform and update participants on the diagnostic services offered and to answer questions.

HIV Testing: Rapid HIV Antibody testing for all participants will take place according to Uganda MoH policy and using the MoH HIV testing algorithm [54]:

1. Initial rapid HIV test
2. All negative results will be informed of their HIV-negative status
3. All positive results will be confirmed with a second rapid HIV test, performed either in series or in parallel with the first test.
4. Discordant results (first test positive, second test negative): participants with discordant rapid tests will undergo a third "tie- breaker" HIV rapid test. Participants with a positive "tie-breaker" test will be informed that they are HIV positive. Participants with a negative "tie-breaker" test will be told that their results are negative.
5. All participants with two confirmed rapid HIV antibody tests will undergo phlebotomy for HIV viral load measurement in a study laboratory.

Non-HIV Health Services: The following services, delivered according to MoH guidelines (and many of which we have implemented in prior studies [28, 53] and the ongoing SEARCH Trial), may be offered at study HIV testing sites at enrollment and during HIV retesting visits:

- *Recommended:* Finger-stick blood glucose measure
- *Recommended:* Syphilis screening (RPR)
- *Recommended:* Blood pressure measurement
- *Recommended:* HIV-infected participants: HIV RNA ("viral load") and point-of-care CD4 cell count testing
- *Recommended:* Malaria rapid diagnostic test (RDT) participants with objective fever ( $\geq 38.5$  degrees Celsius)
- *Recommended:* TB screening (sputum collection for microscopy, *Mycobacterium tuberculosis* culture, or other Uganda MoH approved sputum tests) for all individuals.

Post-test Counseling: All participants, regardless of test results, will receive post-test counseling. Individuals who test HIV positive will be immediately offered referral to a clinic that provides ART and counseled as per Uganda MOH guidelines.

Post-test Questionnaire: Participants who come for repeat testing (i.e. 3-4 months and 6-7 months after baseline HIV testing) will be asked to participate in a questionnaire to understand their reasons for retesting. Participants who do not retest for HIV at the 6-month study visit will be contacted, and visited at home or a place of their choosing, and asked to participate in a short questionnaire to understand their reasons for not retesting and to offer follow-up HIV testing, within 12 months of randomization.

### 8.6.2 Qualitative interview

In-depth semi-structured interviews: We will conduct semi-structured interviews on proportion of study participants in each study arm and subgroup. These interviews will seek to understand the *mechanisms* through which incentives succeeded or failed.

The interview guide will elicit participants' perceptions, attitudes, and preferences related to incentives, including deposits, and psychosocial and contextual factors that influence participants' responses to these incentives and the decision whether or not to retest for HIV.

## 8.7 Data Management and Statistical Considerations

### 8.7.1 Data Collection & Management

Staff will record all study questionnaire data, participant digital fingerprint biometric measurements, HIV test results, and clinic data under each participant's study identification number (ID) in either paper lab logs or password-protected study computers. In-depth semi-structured interviews may be audio recorded. Data from these logs or devices will be entered and transferred via a secure electronic transfer to our data center facility in Kampala and stored on a secure server.

### 8.7.2 Analysis

Primary analysis:

- (a) **HIV retesting uptake:** We will compare HIV retesting uptake (defined as the proportion of participants retesting for HIV at both 3- and 6-month study visits) between the study groups. We hypothesize that HIV retesting uptake among participants offered loss aversion incentives will be higher than uptake among men offered no incentive, and higher than uptake among men offered gain-framed incentives. We will test for significant differences in HIV retesting uptake between the following groups using the 2-tailed  $\chi^2$  analysis or other appropriate statistical methods: a) loss aversion vs. gain-framed incentive; b) loss aversion vs. no incentive; and c) gain-framed vs. no incentive.

Secondary analyses:

- (b) **HIV re-testing uptake at 3-months:** We will compare the proportion of participants who retest for HIV at the 3-month study visit between the study groups. We will test for significant differences in HIV retesting uptake between the following groups using the 2-tailed  $\chi^2$  analysis or other appropriate statistical methods: a) loss aversion vs. gain-framed incentive; b) loss aversion vs. no incentive; and c) gain-framed vs. no incentive.
- (c) **HIV re-testing uptake at 6-months:** We will compare the proportion of participants who retest for HIV at the 6-month study visit between the study groups. We will test for significant differences in HIV retesting uptake between the following groups using the 2-tailed  $\chi^2$  analysis or other appropriate statistical methods: a) loss aversion vs. gain-framed incentive; b) loss aversion vs. no incentive; and c) gain-framed vs. no incentive.
- (d) **HIV retesting uptake among deposit contract group participants who make deposits.** We will compare HIV retesting uptake as described for the Aim 3 primary analysis (above), but restrict the deposit contract group participants to the subset who make deposits at baseline and at the 3-4 month study visit. Since this subgroup is likely to be self-selected on the basis of their desire to come for retesting, we will determine the causal effect of the deposit contract on the likelihood of coming for

retesting using instrumental variables analyses in which randomization to the deposit contract group serves as an instrumental variable for a participant's decision to make a deposit.

- (e) **Cumulative HIV incidence:** We will compare the proportion of participants who test HIV antibody positive within 7 months of participant randomization in each of the study groups using 2-tailed  $\chi^2$  tests or other appropriate statistical methods. We hypothesize that the proportion of newly diagnosed HIV antibody positive participants will be higher in the control group, due to failure to participate in retesting for HIV.

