### 8.7.3 Sample Size & Accrual

We anticipate that about 30% of participants in the control group will come for retesting at both 3 and 6 months. With a sample size of 525 participants randomized 1:1:1 to the 3 study arms, we will have >80% power ( $\alpha=0.05$ , 2-sided) to show a difference of at least 15% in retesting rates in each of the intervention groups compared to the control group. With this sample size there will be >90% power to show a difference of at least 18% between the intervention and control groups.

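### Aim 3 primary analysis: the only named test is a crude chi-square; storing the prior-year HIV test count and prespecifying adjustment for it would add modest precision at little cost

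*Protocol*

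**What the plan says.** **Primary test.** Section 8.7.2, primary analysis (a), compares the proportions who retest at both the 3- and 6-month visits: "We will test for significant differences in HIV retesting uptake between the following groups using the 2-tailed" chi-square. The same sentence leaves room for another suitable method. It lists three pairwise comparisons: loss aversion vs gain-framed, loss aversion vs no incentive, and gain-framed vs no incentive. No covariate or stratification factor is mentioned.

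**Baseline information.** Exclusion (b) in section 8.1.3.2 removes people who have tested for HIV three or more "times in the 12 months prior to recruitment, by self-report". Under Predictors and mediators, section 8.6 states: "Participants' demographic and socio-economic characteristics, as well as HIV risk behaviors, will be recorded at the time of the baseline HIV test". None of the analyses in section 8.7.2 names a use for these variables.

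**Sample size.** Section 8.7.3 works from crude proportions: "We anticipate that about 30% of participants in the control group will come for retesting at both 3 and 6 months". For 525 people split equally over three arms, power above 80% is claimed (two-sided 5%) "to show a difference of at least 15% in retesting rates in each of the intervention groups compared to the control group", and above 90% for 18 points. No power is given for loss aversion vs gain-framed.

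**The concern.** Anyone enrolled in Aim 3 has, by self-report, tested zero, one or two times in the past year. Recent testing is a plausible predictor of later testing, and the question precedes randomisation. A comparison of crude proportions makes no use of it, nor of the other recorded predictors. Adjusting for a prognostic baseline variable normally tightens the estimate and removes chance imbalance in that variable without enrolling anyone extra.

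The protocol accepts adjustment elsewhere: the Aim 2 secondary analysis in section 6.6.2 is a logistic regression adjusted for socio-economic status.

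At stake is some precision in all three primary comparisons, in a trial sized only a little above its 80% target. One part is also time-critical. If the count is not stored at enrolment, no later analysis plan can recover it.

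**Working it through.** **Inputs from section 8.7.3.** 525 / 3 = 175 per arm; control uptake 30%; differences of 15 and 18 points; two-sided alpha 0.05.

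**Step 1: reproduce the stated power.** With d the difference and p̄ the mean of the two proportions,

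power = Φ{ [d − 1.96·√(2p̄(1−p̄)/n)] / √[(p₁(1−p₁) + p₂(1−p₂))/n] }.

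- 30% vs 45%: p̄ = 0.375. √(2 × 0.375 × 0.625 / 175) = 0.0518 and √((0.21 + 0.2475)/175) = 0.0511. Then (0.15 − 1.96 × 0.0518)/0.0511 = 0.950 (unrounded terms), so power is **82.9%**.
- 30% vs 48%: the same steps give 1.518, so power is **93.6%**.

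Both claims hold without adjustment. The margin at 15 points is small: 163 per arm are needed for 80%, or 176 with a continuity correction (power 79.9% at 175).

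**Step 2: what the count could explain (assumed).** The protocol gives no association. Assume equal thirds with 0, 1 and 2 prior tests and overall control uptake of 30%. Then R² = [mean of (pₖ − 0.30)²]/(0.30 × 0.70).

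- 25/30/35%: 0.00167/0.21 = 0.008
- 20/30/40%: 0.00667/0.21 = 0.032
- 10/30/50%: 0.02667/0.21 = 0.127

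**Step 3: effect on power for 30% vs 45%.** Approximate adjustment by an effective n of 175/(1 − R²).

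| R² | Effective n per arm | Power |
|---|---|---|
| 0 | 175 | 82.9% |
| 0.01 | 177 | 83.3% |
| 0.03 | 180 | 84.0% |
| 0.05 | 184 | 84.8% |
| 0.10 | 194 | 86.6% |

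In enrolment terms, R² = 0.05 is worth 525/0.95 − 525 ≈ 28 participants, and R² = 0.10 is worth 525/0.90 − 525 ≈ 58.

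**Step 4: simulation check.** Crude chi-square against Cochran-Mantel-Haenszel stratified by the count, 20,000 runs per scenario, with uptake 15 points higher in every stratum of the incentive arm:

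| Control uptake by 0/1/2 tests | R² | Crude | Stratified |
|---|---|---|---|
| 25/30/35% | about 0.01 | 83.2% | 83.0% |
| 20/30/40% | about 0.03 | 83.5% | 83.8% |
| 10/30/50% | about 0.13 | 83.5% | 87.0% |

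Type I error was 4.9% to 5.1% for both tests. With a count unrelated to retesting, stratified power was 82.8% against 83.3% crude, a loss of about half a point.

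**Step 5: loss aversion vs gain-framed (rates assumed).** For 45% vs 55% the Step 1 formula gives 46.4%. At R² = 0.10 (effective n 194) it gives 50.5%. The unpooled-variance version gives about 47% and 51%.

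**The case against.** The case on the other side is substantial.

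- **The method is not fixed.** Section 8.7.2 allows another suitable method, so a reader who infers that the protocol commits to an unadjusted analysis goes further than the text. Covariates are commonly chosen in an analysis plan, and that document is not shown. This stands. What remains is that crude chi-square is the only test named for a primary endpoint and that a better one can be named.
- **Nothing stated is wrong.** The chi-square is valid under randomisation and the power claims reproduce. This stands in full.
- **The count is not the outcome measured at baseline.** It is tempting to treat it so. But it is a self-report over 12 months at any venue, whereas the outcome in section 8.6 is fingerprint-linked testing at a study site in two set windows. Enrolment also narrows its range: three or more tests is an exclusion, and inclusion (c) in section 8.1.3.1 requires stated willingness to retest. Its predictive value may be weak.
- **The count may not be kept.** Exclusion (b) needs only a yes/no answer at three or more, and section 8.6 does not list testing history among the recorded variables. This stands, and it is why storing the count is part of the fix.
- **The size of the gain is assumed.** A reader might infer about nine points by taking a correlation of 0.5 (R² = 0.25, power 92.0%). Nothing in the protocol supports that value. Even the steep 10/30/50% gradient gives only R² of about 0.13.

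**Conclusion.** This is an optional efficiency improvement, not an error. The protocol's primary test is sound and its Aim 3 power statements are correct as far as they go.

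On the assumption that the count alone explains 1% to 13% of outcome variance, power for 30% vs 45% at 175 per arm goes from about 83% to between 83% and 87%. That is a gain of roughly 0 to 4 points, against a possible loss of about half a point if the count is not prognostic. Other recorded predictors might add to this by an amount the protocol gives no means of estimating.

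Two stronger conclusions are not supported. The documents do not show that precision is lost in all three comparisons, because the method is left open and no association is given. Nor would adjustment secure adequate power for loss aversion vs gain-framed if that difference is smaller than 15 points. The unstated power for that contrast is a separate matter.

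**What to change.** 1. On the Aim 3 screening form, store the number of HIV tests in the prior 12 months (0, 1 or 2), not only whether it reached three.
2. In section 8.7.2, name one primary analysis in place of the open-ended alternative. It can be a covariate-adjusted risk difference from a logistic model with standardisation, or a Cochran-Mantel-Haenszel test stratified by the count. If the model is used, add a short prespecified list of recorded predictors such as age and sex.
3. Keep the crude chi-square as a supporting analysis. Section 8.7.3 can stay on crude proportions.

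The cost is one stored field and a few sentences of analysis text. There is no extra enrolment and no new visit. The statistical risk is the half-point of power lost if the count turns out not to predict retesting.
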